### Statistical methods

Analysis of covariance will be used to evaluate the CEQ scores at T1 between the intervention and control groups with CEQ score at T0 as the covariate. The first eight secondary outcomes will be analyzed with analyses of covariance in analogy to the primary outcome. The last two secondary outcomes will be reported with descriptive statistics. Intention-to-treat analyses with multiple imputations to replace missing data as well as per-protocol analyses will be conducted.

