The second set of videos consists of explanatory videos with explicit explanations of concepts, terms, therapies, and other relevant aspects of rehabilitation. This information is presented by fictional experts from different occupation groups working in inpatient rehabilitation. The roles of the experts are performed by actors and staff from the study center on the basis of the scripts previously created by the psychologists of the study center. All topics included in the scripts have been reviewed and revised by corresponding experts in two cooperating clinics and the German Statutory Pension Insurance.

The user can freely choose the videos of both sets. Participants of the intervention group will get access to the IP after they have given their informed consent. Access will expire when subjects are admitted to inpatient rehabilitation.

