### Control condition

The control group receives no intervention in addition to the usual inpatient rehabilitation preparation (“as usual”). The preparation contains written information about inpatient psychosomatic rehabilitation and a link to the homepage of the respective clinic.

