### Assessment

Assessments will be conducted at study inclusion (T0), two weeks before admission to (T1), and at the end of inpatient rehabilitation (T2; see Fig. 1). Questionnaires at T0 and T1 will be given online. At T2 questionnaires can also be administered in paper and pencil form. At T0 patient characteristics like family status and employment will be assessed together with the patient’s history of pre-treatment. Their Internet use will be ascertained as well. The following instruments are used at each time point. The short form of the Patient Health Questionnaire-4 (PHQ-4) [25] will be used to measure depression and anxiety. The mental condition will be assessed at each time point with the Indicators of Rehabilitation Status (IRES-24) [26]. Additionally, patients’ ability to work will be assessed with the Subjective Prognosis of Work Capacity (SPE) [27]. To measure the patient’s expectancies, the Credibility Expectancy Questionnaire (CEQ) [28] will be given at T0 and T1. Furthermore, the Work-Related Therapy Motivation Questionnaire (FBTM) [29], the Questionnaire for Assessment of Rehabilitation Expectancy and Motivation (FREM-17 [30]), and the Patient Questionnaire for Assessment of Rehabilitation Motivation-20 (PAREMO-20 [31]) will be used to assess work-related therapy motivation and treatment motivation at T0 and T1 as well. The use of the IP and websites with clinic reviews and ratings as well as the clinic websites will be measured only at T1. Patients will be asked about their satisfaction with inpatient treatment at T2. All questionnaires and the time points at which they are administered are displayed in Table 1.

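### The rule that splits the secondary outcomes into eight by ANCOVA and two descriptive does not fit the order of the outcome list or the assessment schedule

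*Protocol article*

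**What the plan says.** The template is the primary analysis. In the Statistical methods section of the protocol article it is an ANCOVA that takes the T0 value of the same score as its covariate: "Analysis of covariance will be used to evaluate the CEQ scores at T1 between the intervention and control groups with CEQ score at T0 as" [...]. Secondary outcomes are then divided by their place in the list: "The first eight secondary outcomes will be analyzed with analyses of covariance in analogy to the primary outcome", and "The last two secondary outcomes will be reported with descriptive statistics".

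The list itself is in the Outcomes section. The measurement times are in the Assessment section and Table 1:

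- Platform use: "The use of the IP and websites with clinic reviews and ratings as well as the clinic websites will be measured only at T1".
- ZUF-8: "Patients will be asked about their satisfaction with inpatient treatment at T2". Table 1 marks it at T2 only.
- IRES-24: "The mental condition will be assessed at each time point with the Indicators of Rehabilitation Status (IRES-24"). Table 1 marks it at T0, T1 and T2.

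On who sees the videos, the Intervention section says "Participants of the intervention group will get access to the IP after they have given their informed consent". The Control condition section says "The control group receives no intervention in addition to the usual inpatient rehabilitation preparation".

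**The concern.** A rule that works by list position is safe only if the list was ordered with the rule in mind. Here a platform-evaluation outcome sits among those to be modelled, and a clinical outcome at the end of rehabilitation sits among those only to be described.

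Three things are at stake. For platform satisfaction and use, the prescribed comparison would set people who were offered the videos against people who were not, adjusted for a baseline that was never taken. The result would have no useful meaning. Multiple imputation is planned for missing data, and read literally it could even fill in control patients' opinion of material they never saw. For ZUF-8, the analyst must choose a covariate that the text does not name. For IRES-24 functioning, a treatment-outcome measure has no planned model-based comparison of arms, although the Background and Discussion say the trial will examine whether preparation improves treatment outcome. An ANCOVA added later would be an unplanned test of a key secondary outcome.

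**Working it through.** No sample-size or power formula bears on this point. The check is to number the Outcomes list in printed order, apply the rule, and compare each entry with the Assessment section and Table 1.

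| No. | Outcome and time | T0 value of the same measure? | Method under the rule | Fit |
|---|---|---|---|---|
| 1 | FBTM, T1 | yes | ANCOVA | fits |
| 2 | FREM-17 and PAREMO-20, T1 | yes | ANCOVA | fits |
| 3 | CEQ credibility, T1 | yes | ANCOVA | fits |
| 4 | Platform satisfaction and use, T1 | no | ANCOVA | does not fit |
| 5 | IRES-24 mental condition, T2 | yes | ANCOVA | fits |
| 6 | ZUF-8, T2 | no | ANCOVA | covariate undefined |
| 7 | SPE, T2 | yes | ANCOVA | fits |
| 8 | PHQ-4, T2 | yes | ANCOVA | fits |
| 9 | IRES-24 functioning, T2 | yes | descriptive | inconsistent with no. 5 |
| 10 | Perceived advantage of aftercare, T1 and T2 | no instrument named, no row in Table 1 | descriptive | no objection |

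**The plan's own figure.** 8 + 2 = 10, and the list has 10 entries. The positions are therefore unambiguous, and the mismatch is not a miscount.

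**First eight.** Nos. 1, 2, 3, 5, 7 and 8 have a T0 score, so 6 of 8 can take the primary-type model. Nos. 4 and 6 cannot take it with their own baseline.

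**Last two.** No. 9 has a T0 score. No. 10 has none in the schedule.

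**Totals.** 6 + 1 = 7 of 10 outcomes have a T0 score of the same instrument. The rule is out of line with the schedule for 3 of 10 (nos. 4, 6 and 9), in three different ways:

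- No. 4 lacks a T0 value, and the object being rated is open to one arm only. No choice of covariate repairs the second problem.
- No. 6 lacks a T0 value because patients cannot rate a stay that has not begun. Both arms do have a T2 value, so a comparison is possible.
- No. 9 has the same instrument and the same measurement times as no. 5, but a different method, and no reason is given.

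**Limit of the check.** Table 1 has a row for platform use but none for satisfaction with the platform. For satisfaction, the T1-only timing rests on the Outcomes list.

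**The case against.** The strongest reply is that only no. 4 is a plain misassignment.

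*ZUF-8.* The rule asks for analysis by analogy and does not say that each outcome is adjusted for its own baseline. The one covariate named is CEQ at T0, which both arms have. An ANCOVA of ZUF-8 on that or another T0 score can be run, and the choice of covariate is a detail that an analysis plan may settle. This stands. A reader might infer that two of the prescribed analyses are impossible, but the document does not support that for ZUF-8, where the covariate is simply not defined.

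*IRES-24 functioning.* Reporting a secondary outcome descriptively is permissible, and nothing obliges the trial to test everything that has a baseline. The Sample size calculation section also says effect sizes will be calculated to describe treatment effects, without restricting this to tested outcomes. This stands in part. It would be too strong to say that functioning will have no estimate of the arm difference. It would also be too strong to say that the treatment-outcome aim is lost, because nos. 5, 7 and 8 are still modelled at T2. What remains is an unexplained difference between two outcomes from one questionnaire.

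*Controls and the platform.* All patients log in to consent, the T0 and T1 questionnaires are given online, and Table 1 does not limit the platform-use row to one arm. It would therefore be wrong to say that controls have no contact with the platform. What they lack is the video content. At most this gives a control value for login pages or a structural zero for videos, and a T0 value is still absent.

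*Left to an analysis plan.* This does not dispose of the point. The article states an explicit rule, and for no. 4 an analysis plan could put it right only by departing from that rule.

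**Conclusion.** The point holds in a limited form. Three of ten key secondary outcomes are poorly served by the counting rule, to different degrees: no. 4 is assigned an analysis without a meaningful result, no. 6 has an undefined covariate, and no. 9 has no planned model-based comparison although its data support one and its companion outcome receives one. It would overstate the case to say that all three have a wrong method.

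The primary analysis of CEQ at T1 is untouched, and so is the FBTM hypothesis (no. 1). This should be corrected, but it does not threaten the trial's main inference.

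The conclusion assumes that the printed order of the Outcomes list is the order the rule refers to, which the count of ten supports. It also assumes that the analogy with the primary outcome means adjustment for a T0 score, as the primary model is described.

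**What to change.** Replace the two counting sentences with a statement that names each outcome and its method:

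- **ANCOVA on the outcome's own T0 score:** FBTM, FREM-17, PAREMO-20, CEQ credibility, IRES-24 mental condition, IRES-24 functioning, SPE and PHQ-4.
- **Comparison of arms without its own baseline:** ZUF-8 at T2, with one available T0 covariate named in advance or with none.
- **Descriptive:** satisfaction with and use of the platform, in the intervention arm, and perceived advantage of aftercare.

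The cost is about two sentences of text and one additional ANCOVA. All the data needed are already in the schedule, and no new assessment is required. The change should be made before outcome data are seen by arm. Adding clinic as a covariate, since randomization is stratified by clinic, is a separate and optional improvement on which this point does not depend.

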## Discussion

Patients’ expectations are known key factors in psychotherapy. Several studies have confirmed the influence of patients’ expectations on the therapy outcome. Moreover, it is known that expectations can be specifically influenced, e.g., by providing a good and convincing treatment rationale [35]. Thus, not only expectations as a key factor but also the therapy outcome itself can be influenced by preparation. Although this could offer an easy way to enhance the results of psychotherapy, the few intervention studies in Germany which have investigated the influence of preparation on patients’ expectations and therapy outcome showed mixed results [14, 17, 18].

In line with previous findings [20, 35], we expect a targeted intervention based on video clips embedded in a virtual online clinic format to enhance positive and realistic patients’ outcome expectations and thereby improve treatment participation and outcome. Studying the connection between an emotional approach and a greater effectiveness in recognition, Cahill et al. [36] showed that emotional video clips were remembered more often than neutral videos. Therefore, we deliberately chose a video-based approach with actors and scripted patient stories conveying common disorders and targeted information about the treatment process, measures, roles of patients and therapists, and treatment outcomes in an emotional and personal way.

We wanted to design our intervention in a modern and trendsetting way to enhance the chances for continuation and dissemination if it proves to be effective. To verify our assumption that videos are an appropriate and well-accepted medium to convey information, we will collect objective data in addition to the data assessed by questionnaires. Therefore, patients’ user behavior will be tracked on the platform and linked with the treatment results. Tracking includes the time spent on the website, the number and types of videos, and the duration of all videos watched by each patient.

Overall, our intervention will use a novel and highly advanced approach to prepare rehabilitants for their inpatient treatment. We intend to determine if such a modern approach can improve patients’ expectations and the treatment outcome. If our intervention proves to be effective, it could be used as a blueprint for a new preparation method for psychosomatic rehabilitants in Germany. It could be used along with the usual written information every patient receives before his admission to inpatient rehabilitation. It would easily be possible, though, to adjust the design to fully substitute the written information. It is also imaginable that the intervention can be adopted for other treatments, like psycho-oncology or orthopedic or cardiovascular diseases. In summary, this trial will provide further insight into the process of preparing patients properly for psychosomatic rehabilitation, which is the most common inpatient psychotherapeutic treatment option in Germany. This is an important approach, particularly against the background of an increasing number of people diagnosed with mental disorders in Germany.

### Trial status

The first patients will be enrolled to the study in September 2015. Assessments for the last included patients are expected to be completed by August 2016.

## Abbreviations

CEQ, Credibility Expectancy Questionnaire; FBTM, Work-Related Therapy Motivation Questionnaire; FREM-17, Questionnaire for Assessment of Rehabilitation Expectancy and Motivation; IP, Internet platform; IRES-24, Indicators of Rehabilitation Status-24; PAREMO-20, Patient Questionnaire for Assessment of Rehabilitation Motivation-20; PHQ-4, Patient Health Questionnaire-4; SPE, Subjective Prognosis of Work Capacity; ZUF-8, Patient Satisfaction Questionnaire-8; BADO, Basis documentation
